### Outcomes measures

#### Demographic information

Patients will self-report a variety of demographic and descriptive information *via* paper forms, including age, sex, comorbidities, medications commonly used, duration of symptoms, marital status, employed status, educational level, and economic income. Weight and height will be measured at the beginning of the assessments.

The social determinants will be categorized as follows: (I) employment status: employed *versus* unemployed; (II) educational level: participants will assigned to the lower educational level if they had not completed secondary education and to the higher educational level if they had completed secondary education or university studies (Núñez Cortés et al., 2023a; Nuñez Cortés et al., 2023b); (III) economic income will be categorized according to individual monthly taxable income. The cut-off point will be set at a value equal to or less than USD 545, which determines the degree of coverage provided by the Chilean public health system.

### Primary outcomes

#### Fear avoidance and beliefs

This variable will be evaluated with the Fear Avoidance Beliefs Questionnaire (FABQ). The FABQ presents a minimum detectable change of 5.4 for the physical activity subscale and 6.8 for the work subscale (George, Valencia & Beneciuk, 2010). The minimal clinically important change (MCID) is 4 points for the FABQ-Physical Activity scale (FABQ-PA) and 7 points for the FABQ-Work scale (FABQ-W) (Monticone et al., 2020). Its Spanish version has been validated with a high internal consistency (Cronbach *α* = 0.933) with good test-retest reliability (ICC = 0.966) (Kovacs et al., 2006). Higher scores indicate higher levels of fear avoidance beliefs (George, Valencia & Beneciuk, 2010).

### Secondary outcomes

#### Algometry

An algometer will be used to measure pressure pain sensitivity. The average of three measurements will be used (Nussbaum & Downes, 1998; Christidis, Kopp & Ernberg, 2005). This method has excellent test-retest reliability (ICC = 0.80–0.99) within a session and between sessions (ICC = 0.87–0.95) (Potter, McCarthy & Oldham, 2006). It also presents good to excellent inter-evaluator reliability (ICC = 0.74–0.89) (Nussbaum & Downes, 1998). The minimum significant change has been reported at ≥1.16 kg/cm^2^/s (Fuentes et al., 2011). Patients will be evaluated lying down in a comfortable position according to the area to be evaluated with a digital algometer (WAGNER FDX10). A gradual increase in pressure of 1 kg/cm^2^/s will be applied bilaterally at five cm lateral to the spinous process of L3, in the second metacarpal and the tibialis anterior muscles with the aim of examining changes in generalized sensitivity to pressure pain (Roussel et al., 2013). Between each repetition there will be a rest of approximately 30 s.

#### Pain self-efficacy

The pain self-efficacy questionnaire (PSEQ) will be used to assess this variable (Koenig et al., 2014). It has a high internal consistency (Cronbach *α* = 0.92) (Nicholas, 2007), high test-retest reliability (ICC = 0.86) and a minimal clinically important difference between 5.5 and 8.5 points (Dubé, Langevin & Roy, 2021). Higher scores indicate stronger self-efficacy beliefs, while low scores indicate a subject more focused on their pain.

#### Catastrophizing

Catastrophizing will be evaluated by applying the Pain Catastrophizing Scale (PCS) (Burri et al., 2018). In a population with chronic pain, has a high total internal consistency (Cronbach *α* = 0.92), a moderate total test-retest reliability (ICC = 0.73) (Lamé et al., 2008), and is validated in Spanish (García Campayo et al., 2008).

#### Pain intensity

Pain intensity will be measured with the Numerical Rating Scale (NRS) since it presents minimal translation difficulties, which allows its use in all cultures and languages (Karcioglu et al., 2018). The NRS presents, in patients with chronic lumbar pain, an excellent test-retest reliability (ICC = 0.92), a standard error of measurement of 0.86, a minimum detectable change of 2.4 points, and a clinically important minimum change of 4 points (Maughan & Lewis, 2010). The intensity at rest and activity in the last 7 days will be considered.

#### Treatment expectation

The treatment expectation questionnaire (TEX-Q) will be used. This is a generic multidimensional measure that allows evaluating the patient’s expectations in both medical and psychological treatments and allows comparing the impact of multidimensional expectations in different conditions. Its psychometric properties have yet to be determined, but it was developed through a rigorous procedure that incorporated complex and diverse literature and expectation evidence as well as peer review (Alberts et al., 2020).

#### Sample size

Sample size calculation was performed with G*Power 3.1. A repeated measures analysis of variance (ANOVA) model with within-between interaction, was used. Assuming an alpha risk of 0.05, a power of 0.95, a correlation between repeated measures of 0.5, a 10% drop-out rate, and a small effect size (0.26), a total of 20 participants per group (three groups) were required. The effect size estimate was based on a previous study about education compared to physical therapy for the FABQ outcome (Marshall et al., 2022) and the recommended effect size for clinical studies (Lakens, 2013).

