### Study objectives

The objectives of this trial are: (1) to compare the clinical and psychosocial effectiveness of in-group modality and individual modality of pain neuroscience education (PNE) in patients with CLBP; (2) To analyze the influence of social determinants of health on post-treatment results.

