#### Randomization and blinding

Participants will be randomized in a 1:1:1 ratio between intervention and control arms using balanced group assignment with block randomization with permuted block size. An independent researcher will carry out the process of randomization through a web platform (http://www.randomizer.org) and will allocate concealment from patients and other investigators using sealed, opaque envelopes.

Participants, assessor, and statistician will be blinded to group assignment. Participants will only be informed that they will receive an educational intervention without indicating to which experimental group they will belong; the assessor will not be informed of the group to which the participants belong; and the identification data of the participants will be coded in the database before being sent to the statistician. However, the physical therapist who will perform the educational intervention will not be blinded.

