### Data analysis

#### Statistical approach

The analysis of the data will be blinded, as each subject and condition will be coded by a consultant who will not be involved in the investigation. SPSS software version 25.0 will be used for all analyzes (SPSS Inc. Armonk, NY, USA). Data will be reported as mean with SD or median with interquartile range. Statistical analyzes were performed on an intention-to-treat basis, with imputation of missing data using the average of the remaining participants.

Normality tests will be performed using the Shapiro–Wilk test given the number of subjects needed for each group. In addition, the homogeneity of variance and the sphericity of the data will be determined. In the case of not assuming any of these assumptions, the Green-Hausser correction will be used for the interpretation of subsequent analyzes. A three-way repeated measures ANOVA will be conducted to analyze both primary and secondary outcomes. The factors considered in this analysis will include time and intervention. Additionally, the third factor will encompass variables such as employment status, education level, or income. In case of significant interaction, a two-way repeated measures ANOVA (time (pre-post) × intervention (in-group PNE, individually PNE, no intervention)) will be performed for each employment status (employed or unemployed). Furthermore, a two-way repeated measures ANOVA (time (pre-post) × intervention (in-group PNE, individually PNE, no intervention)) will be performed for each educational level (high or low). Lastly, a two-way repeated measures ANOVA (time (pre-post) × intervention (in-group PNE, individually PNE, no intervention)) will be performed for income (≤USD 545, or >USD 545). If interactions are detected in any of the 2-way ANOVAs, a *post-hoc* analysis will be conducted using multiple pairwise comparisons employing a *t*-test corrected by Bonferroni. The significance level will be set at 5%.

A stepwise multiple linear regression will be performed to estimate the influence of changes in primary and secondary outcomes. In each model, adjustments will be made for employment status, educational level, and income. In this analysis, the aforementioned variables will be sequentially incorporated into each model.

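### The 0.95 power is for a whole-sample time × intervention test that the analysis section never sets out as an analysis of its own; the determinant tests serving Objective 2 are not covered by it

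*Protocol article*

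**What the plan says.** **Sample size.** The calculation is for a time × group interaction: "A repeated measures analysis of variance (ANOVA) model with within-between interaction, was used". The other inputs are alpha 0.05, power 0.95, correlation 0.5 among the measurements and 10% loss to drop-out. The effect size and the result read: "a small effect size (0.26), a total of 20 participants per group (three groups) were required". On the origin of the effect: "The effect size estimate was based on a previous study about education compared to physical therapy for the FABQ outcome". No social determinant enters the calculation.

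**Statistical approach.** The analysis is a different model: "A three-way repeated measures ANOVA will be conducted to analyze both primary and secondary outcomes". Its factors are time, intervention and one of employment status, education level or income. After a significant interaction, a two-way time × intervention ANOVA "will be performed for each employment status (employed or unemployed"), and the same is written for education and income. Bonferroni-corrected pairwise t-tests follow if one of these two-way ANOVAs shows an interaction. A stepwise regression with the three determinants is added.

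**Study objectives.** Objective 1 compares in-group with individual delivery. Objective 2 is: "To analyze the influence of social determinants of health on post-treatment results". The hypothesis in the Introduction covers both.

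**The concern.** The sample size and the analysis describe two different models, and both are fixed in this document.

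- **Objective 1.** The test that was powered is not written as a stand-alone analysis in all participants. The pairwise comparison of the two delivery modes, which is the trial's leading question, comes only after a significant determinant interaction and a significant two-way interaction within a determinant level. If no determinant modifies the effect, the text does not lead to that contrast at all.
- **Objective 2.** The three-way and within-level tests carry no sizing. A reader who sees 0.95 could take a non-significant determinant interaction, or a null result in a low-education stratum, as evidence of no influence. The Discussion presents this question as the knowledge gap.

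**Working it through.** **Inputs from the Sample size section:** f = 0.26 (read as Cohen's f), correlation 0.5, alpha 0.05, three groups, 20 per group (N = 60). Allocation: "Participants will be randomized in a 1:1:1 ratio between intervention and control arms".

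**Inputs on which the document varies:** the follow-up ANOVAs are labelled pre-post (m = 2 time levels), while Data collection and management lists three assessments (m = 3). The Abstract gives 69 in total but also 33 per arm (3 × 33 = 99).

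**Assumptions, because the protocol gives no figure:** share p of the smaller determinant level (50%, 30% or 20%, equal across arms), the size of the interaction, sphericity, and Type III sums of squares.

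**1. The plan's own figure.** λ = f²·N·m/(1 − ρ), with df 2(m − 1) and (N − 3)(m − 1).
- m = 2, N = 60: λ = 0.0676 × 60 × 2 / 0.5 = 16.22; df 2 and 57; power **0.949**. This matches the stated 0.95, but with no allowance for drop-out.
- m = 3, N = 60: λ = 24.34; power 0.984. At 54 completers (60 × 0.9), power is 0.924 (m = 2) or 0.971 (m = 3).

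**2. The same test as a lower-order term of the three-way model.** Type III tests the unweighted mean of the two level-specific effects. With a common effect, λ becomes λ × 4p(1 − p), with df 2(m − 1) and (N − 6)(m − 1).

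| N = 60 | 50:50 | 30:70 | 20:80 |
|---|---|---|---|
| λ, m = 2 | 16.22 | 13.63 | 10.38 |
| Power, m = 2 | 0.95 | 0.905 | 0.81 |
| Power, m = 3 | 0.98 | 0.96 | 0.89 |

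At N = 99 this power is at least 0.96. With three possible third factors, the term exists in up to three versions, and none is named as the primary test.

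**3. Three-way interaction, full effect in one level and none in the other.** The λ is λ × p(1 − p), with df as in step 2. Example: m = 2, 50:50, 16.22 × 0.25 = 4.06.

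| Power | 50:50 | 30:70 | 20:80 |
|---|---|---|---|
| N = 60, m = 2 | 0.40 | 0.34 | 0.27 |
| N = 60, m = 3 | 0.46 | 0.39 | 0.30 |
| N = 99, m = 2 | 0.62 | 0.54 | 0.43 |
| N = 99, m = 3 | 0.71 | 0.62 | 0.49 |

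If the three-way term itself had f = 0.26, its power at N = 60 would be 0.949 (m = 2) or 0.984 (m = 3). At 50:50 the interaction f is half the difference between the two level-specific effects, so that difference would have to be 2 × 0.26 = 0.52. One example is the full effect in one level and its exact reverse in the other.

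**4. Two-way ANOVA within the smaller level.** The formula of step 1 applies with n = N × p. Example: n = 30, m = 2, λ = 0.0676 × 30 × 2 / 0.5 = 8.11.

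| Power | 50% | 30% | 20% |
|---|---|---|---|
| N = 60, m = 2 (n = 30, 18, 12) | 0.67 | 0.41 | 0.26 |
| N = 60, m = 3 | 0.77 | 0.49 | 0.30 |
| N = 99, m = 2 (n = 50, 30, 20) | 0.90 | 0.67 | 0.46 |
| N = 99, m = 3 | 0.96 | 0.77 | 0.55 |

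The larger level does better: at N = 60, m = 2, power is 0.84 with 70% of participants and 0.89 with 80%.

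**The case against.** The strongest reply has four parts.

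- **The powered test is in the model.** A reader might infer that the time × intervention ANOVA is run only inside determinant strata. The text does not support that: the three-way ANOVA uses all participants and has time and intervention as factors. At equal splits its time × intervention term keeps about 0.95. This stands. What remains is that the term is not named as the primary test, loses power when the split is unequal, and has no whole-sample pairwise follow-up.
- **Nothing is miscalculated on this point.** A reader might infer that the protocol claims 0.95 for Objective 2. It does not: it names the interaction it sized. Sizing a trial on its main comparison and not on effect modification is normal practice. This also stands, so the point is a mismatch between sections and not an arithmetic error.
- **The low power figures rest on assumptions.** A reader might attach one low range to all of Objective 2. The documents do not allow it: the three-way and stratum tests differ, and the results move with the split, the interaction size, N and the number of time levels. In the best case here, stratum power reaches 0.96. Even so, an effect in one level and none in the other is already strong modification, and three-way power stays at or below 0.71 in every such case computed.
- **The stepwise regression also serves Objective 2.** That is true, but it is not sized either, so 0.95 does not cover it.

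The protocol states no rule that a non-significant interaction means no influence. That misreading is a risk, not a stated plan.

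**Conclusion.** The point holds as a mismatch between the Sample size and Statistical approach sections. The stated 0.95 reproduces (0.949 at f = 0.26, correlation 0.5, N = 60, two time levels, no drop-out) for a whole-sample two-way interaction that is never written as an analysis in its own right.

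For Objective 1 the loss of power is nil at an even split and moderate at 20:80 (0.81 at N = 60, two time levels). The larger problem is that the comparison of the two delivery modes in all participants has no ungated test.

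For Objective 2, tests of a one-level-only effect have low to moderate power for the three-way term. Power in the smaller stratum runs from 0.26 to 0.96 depending on N, split and number of time levels. The arithmetic is firm. The splits and the interaction size are assumptions, and the conflicting totals (60, 69, 99) leave the final figure open.

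**What to change.** 1. In the Statistical approach section, make the two-way time × intervention ANOVA in all participants, with its Bonferroni pairwise comparisons, the primary analysis for Objective 1. Use the three-way models only for the determinant interaction.
2. In the Sample size section, say that 0.95 applies only to that whole-sample test.
3. Label Objective 2 (three-way, stratum and stepwise regression analyses) exploratory. Report its effects with 95% confidence intervals, and state that a non-significant interaction or stratum is not read as no influence. If power is quoted for these tests, give the assumed split and interaction size with it.

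The cost is wording in two sections, one extra model and a weaker claim for Objective 2. No more patients are needed.

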#### Randomization and blinding

Participants will be randomized in a 1:1:1 ratio between intervention and control arms using balanced group assignment with block randomization with permuted block size. An independent researcher will carry out the process of randomization through a web platform (http://www.randomizer.org) and will allocate concealment from patients and other investigators using sealed, opaque envelopes.

Participants, assessor, and statistician will be blinded to group assignment. Participants will only be informed that they will receive an educational intervention without indicating to which experimental group they will belong; the assessor will not be informed of the group to which the participants belong; and the identification data of the participants will be coded in the database before being sent to the statistician. However, the physical therapist who will perform the educational intervention will not be blinded.

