**Figure 1 fig-1:**
[figure not shown]
The proposed CONSORT diagram of enrollment, allocation, follow-up, and analysis throughout the study for each arm.

The study population will be people diagnosed with low back pain for ≥ 3 months. Participants will be recruited from the clinical center of the Santo Tomás University, through social media and publications health centers in the city of Talca.

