## Discussion

CLBP is considered to be one of the most prevalent health conditions, contributing significantly to the global burden of disease (Rabiei, Sheikhi & Letafatkar, 2021). Therefore, it is relevant to determine cost-effective therapeutic strategies that can improve the clinical condition of patients. In this sense, therapeutic strategies directed by physical therapists based on the biopsychosocial (BPS) model have been shown to effectively improve symptoms in people with spinal disorders (Miki et al., 2023).

PNE is based on the BPS model (Nijs et al., 2011; Moseley & Butler, 2015) and has been shown a to have positive effect on pain, disability, catastrophism, kinesiophobia, physical performance, and a reduction in health care costs in subjects operated for radiculopathy (Louw et al., 2011; Louw et al., 2016a; Gallagher, McAuley & Moseley, 2013; Mittinty et al., 2018). This may be because it influences pain cognitions, an important aspect in the vicious circle of central sensitization in patients with CLBP even when not all present with such sensitization (Huysmans et al., 2018). However, PNE implemented in isolation may not generate significant clinical effects (Louw et al., 2016c; Louw, Puentedura & Zimney, 2016; Puentedura & Flynn, 2016). While PNE performed in a group modality could potentially facilitate learning through social observation, which would provide a positive influence on therapy due to the observation of the behaviors exhibited by other participants (Romm et al., 2021).

The lack of effectiveness of the PNE applied in isolation may be because it has been approached mainly from the neurophysiology of chronic pain with little orientation of the contents to the context of the person. Furthermore, a very small number of studies have considered within the demographic characteristics the educational level of the subjects (Malfliet et al., 2017; Mittinty et al., 2018; Rufa, Beissner & Dolphin, 2018); and of these, only one used this data to be analyzed, however, it was used as a secondary variable and it was evidenced that a high educational level is associated with the expectation of recovery, not with the very effectiveness of the intervention of education (Mittinty et al., 2018), In addition, these studies tended to present more subjects with high educational levels, however, it has been shown that people who are more predisposed to have lumbar pain chronification have a low level of education (Meucci et al., 2013).

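### Educational level is a planned analysis factor, but the blocks are not stratified by it, so the low-education group may fall unevenly across the three arms; comparisons inside that level should be called exploratory.

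*Protocol article*

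**What the plan says.** The second objective reads "To analyze the influence of social determinants of health on post-treatment results". Under Demographic information, three determinants are each split in two: employment, education and income. For education, participants are "assigned to the lower educational level if they had not completed secondary education"; everyone who finished secondary school or went further counts as high.

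Under Statistical approach, a three-way repeated-measures ANOVA takes time, intervention and one determinant as factors. If the interaction is significant, a time-by-intervention ANOVA over the three arms "will be performed for each educational level (high or low"). Regressions with the three determinants as adjusters follow.

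The Discussion says of earlier pain neuroscience education trials that "these studies tended to present more subjects with high educational levels", although "people who are more predisposed to have lumbar pain chronification have a low level of education".

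Under Study design, participants are to be "recruited from the clinical center of the Santo Tomás University, through social media and publications health centers in the city of Talca". Under Randomization and blinding, allocation is made "using balanced group assignment with block randomization with permuted block size". No stratification factor and no block size are stated. The Sample size section covers a time-by-group interaction only and makes no allowance for education.

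**The concern.** Blocking without strata balances the total number per arm. It does nothing for the number of low-education participants per arm. The low category is defined narrowly, so it may be small, and a small group split by chance over three arms is often split unevenly. An arm with two or three such people tells little about whether the education, or the group format, works differently at that level. That is the question the Discussion presents as the gap to be filled. Allocation cannot be repaired after enrolment, and an analysis plan cannot add stratification later, so the point has to be settled in the design.

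**Working it through.** **Inputs from the article.** Alpha 0.05, power 0.95, correlation 0.5, drop-out 10%, f = 0.26, three groups, 20 per group (Sample size). Three assessments (Data collection). Total 69, but 33 in each arm (Abstract). 69/3 = 23 per arm; 3 × 33 = 99; 3 × 20 = 60. These totals conflict, so results are given for 23 and 33 per arm.

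**Input not in the article.** The low-education share p. Assumed 15–30%, with higher values also shown.

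**Step 1. The plan's own sample size.** For the within-between interaction, λ = f²·N·m/(1 − ρ), df1 = (k − 1)(m − 1), df2 = (N − k)(m − 1), with k = 3 groups and m = 3 assessments. At N = 51: λ = 0.0676 × 51 × 3/0.5 = 20.7, df = 4 and 96, power 96%. N = 51 is the smallest multiple of three reaching 95%. With drop-out, 51/0.9 = 56.7, so 57, or 19 per group. The article states 20, so the formula is close enough to use below.

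**Step 2. Expected low-education count per arm (n × p).**
- 23 per arm: 23 × 0.15 = 3.5; 23 × 0.20 = 4.6; 23 × 0.30 = 6.9.
- 33 per arm: 33 × 0.15 = 5.0; 33 × 0.20 = 6.6; 33 × 0.30 = 9.9.

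**Step 3. Imbalance without stratification.** 200,000 simulated trials, count in each arm drawn as Binomial(n, p).

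| n per arm | p | P(some arm ≤ 3) | P(largest ≥ 2 × smallest) |
|---|---|---|---|
| 23 | 15% | 90% | 70% |
| 23 | 20% | 65% | 58% |
| 23 | 30% | 15% | 37% |
| 23 | 40% | 2% | 20% |
| 33 | 20% | 22% | 43% |
| 33 | 30% | 1% | 22% |
| 33 | 40% | under 1% | 9% |

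Fixing the low-education total (14 of 69, or 20 of 99) instead of letting it vary gives 65% and 40% for the twofold imbalance, so the order of magnitude does not depend on the method.

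**Step 4. Imbalance with a list stratified by education.** At 23 per arm and a 20% share, the chance of a twofold imbalance falls from 58% to about 0.3% with blocks of three and about 5% with blocks of six. At 33 per arm it is below 1% with either. The article gives no block size, so both are shown.

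**Step 5. Power inside the low-education level.** Same formula as step 1, 20% share, drop-out ignored, equal arms.
- Total 69: 0.20 × 69 = 13.8, about 14 people. λ = 0.0676 × 14 × 3/0.5 = 5.68, df = 4 and 22, power 37%.
- Total 99: 0.20 × 99 = 19.8, about 20 people. λ = 8.11, df = 4 and 34, power 55%.
- With two assessments (the pre-post wording of the ANOVA), 31% and 46%.

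**Step 6. What stratification adds to that power.** For a difference between the group and individual arms at a 20% share: 39% stratified against 35% unstratified (total 69), and 57% against 52% (total 99). At a 30% share: 57% against 55%, and 77% against 75%. The gain is about 2 to 5 points. (The 39% exceeds the 37% of step 5 because 14 people split 5, 5 and 4, with the larger cells placed in the two arms compared.)

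**The case against.** The strongest reply is that the low-education share is unknown and everything above turns on it. That stands: at 40% the chance of an arm with three or fewer is 2% even at 23 per arm. Unstratified permuted blocks are also a valid scheme and contradict nothing in the article. The full protocol is a supplement not shown here; if it names education as a stratum, the allocation half of this point falls away.

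Several stronger readings are tempting, and the article does not support them.
- *The sample will be skewed to the better educated because it comes from a university.* The site is a treatment clinic, eligibility is age 45–60, and health centres in Talca are a third recruitment route. Nothing prevents a skew, but nothing shows one.
- *Chance imbalance in education confounds the overall arm comparison.* Under randomisation it adds noise, not systematic bias. An effect that differs by education is effect modification. Education is already a factor in the ANOVA and an adjuster in the regressions.
- *The second objective depends wholly on comparisons inside the low level.* The three-way ANOVA and the regressions use the whole sample, and the level-specific ANOVAs run only after a significant interaction. That interaction does rest on the same small cells, however.
- *An enrolment quota is required.* Its feasibility depends on the unknown share. One third of 69 is 23 people, for whom the step 1 formula gives about 62% power, still well short of 95%.

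**Conclusion.** The point holds as a cheap, specific improvement to allocation, together with a limit on what may be claimed. The article gives education a planned role in the analysis and leaves its balance across arms to chance. If the share is about 20%, a twofold imbalance in the low-education level is more likely than not at 23 per arm and occurs in about four trials in ten at 33 per arm. Stratification nearly removes it. Stratification does not cure the low power inside that level, because power is set by the number of low-education participants and not by how they are divided. The sizes rest on an assumed share, on the article's f and correlation, and on which of the conflicting totals applies. The validity of the overall comparison between arms is not in question.

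**What to change.** Stratify the permuted-block list by educational level (secondary education completed: yes or no), and record the answer before the envelope is opened. Keep blocks small, since unfilled blocks are what leave residual imbalance. The cost is two lists and two sets of envelopes instead of one; the item is already on the baseline form and no more patients are needed.

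In the Statistical approach section, describe the comparisons within each education level as exploratory, reported as estimates with confidence intervals. This costs only wording.

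Reconcile the totals of 69, 99 and 60, since the expected cell sizes depend on them. A minimum number of low-education participants is an option for the investigators to weigh, and is not needed for this fix.
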